### Sample size

The sample size calculation is based on changes in lifestyle behaviors and health outcomes, for which we used data from a previous study on inpatients in the Netherlands [19]. A sample size of 98 participants is necessary to detect an average effect (f^2^ = 0.15) in a linear regression analysis with 80% power, 95% confidence interval, and six variables in the model. After reaching consensus on feasibility with the collaborating region, it was decided to enroll 50 people to participate in the GOAL! program and recruit an equally sized control group.

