#### Mental health outcomes

##### Psychiatric symptoms

The Brief Symptom Inventory (BSI) is used to assess psychiatric symptoms. The BSI consists of 53 items covering 9 symptom domains of the SCL-90-R, examining scores for 9 symptom dimensions: somatization, obsession-compulsion, interpersonal sensitivity, depression, anxiety, hostility, phobic anxiety, paranoid ideation, and psychoticism. Each item is assessed via a 5-point Likert scale, ranging from 0 (not at all) to 4 (extremely) [54]. The BSI is reliable and its validity is supported across patient groups with various diagnoses in a Dutch sample [55].

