**Intervention and control group**						
T0	Demographic characteristics	Gender	Categorical		x	
		Nationality	-		x	
		Ethnicity	Categorical		x	
		Date of birth (age)	Years		x	
		Diagnosis	Categorical		x	
		Marital status	Categorical		x	
		Highest level of education	Categorical		x	
		Primary source of income	Ratio		x	
T0, T1, T2, T3	Physical activity and sedentary behavior	Simple Physical Activity Questionnaire (SIMPAQ)	Moderate-vigorous physical activity in min/week and sedentary time per day	x		
	Eating behavior	MijnEetmeter	Daily intake of nutrients and daily consumption according to the Dutch ’Wheel of Five’		x	
	Sleep	Scales for Outcomes in Parkinson’s Disease sleep (SCOPA-sleep)	Total scores for nighttime sleep quality and daytime sleepiness	x		
	Substance use	Alcohol, Smoking and Substance Involvement Screening Test Lite (ASSIST-Lite)	Total scores of tobacco, alcohol, cannabis, stimulants, sedatives and opioids and psychoactive use	x		
	Physical health	Weight	kg	x		
		Abdominal circumference	cm	x		
		BMI	kg/m^2^	x		
		Fat percentage	%	x		
		Blood pressure	mmHg	x		
	Psychiatric symptoms	Brief Symptom Inventory (BSI)	Total scores for 9 symptom dimensions: somatization, obsession-compulsion, interpersonal sensitivity, depression, anxiety, hostility, phobic anxiety, paranoid ideation and psychoticism		x	
	Quality of life	Euro-Qol-5D-3 L (EQ-5D-3 L)	Index score based on the Dutch tariff and VAS score		x	
T0, T3	Care and social costs	Treatment Inventory of Costs in Patients with psychiatric disorders (TIC-P)	Healthcare utilization, medication use, productivity loss and costs (€)		x	

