### Statistical analysis

To assess the effect of GOAL! on lifestyle behaviors and health outcomes, data will be analyzed via multiple linear regressions and linear mixed models (LMMs). LMMs allow for testing the effect over time (four measurement points) and accounting for potential clustering (e.g., participant groups). In all analyses, the treatment condition (GOAL! participants vs. control group, coded as 1/0) will be the independent variable, and the outcomes measures will be the dependent variables, with physical activity (in minutes per week) as the primary outcome. All analyses will be adjusted for potential confounders, such as age (continuous), sex (male vs. female, coded as 0/1), key diagnostic subgroups (categorial, added as dummy variables), baseline values (continuous), session adherence (continuous), and changes in medication use (continuous).

When necessary, missing data will be addressed through multiple imputations via the MICE package in R. When constructing the imputation model, we will include the variables used as predictors in our analysis. The number of imputations and iterations will be based on the proportion of missing data in our LMM. Results from imputed datasets will be pooled using Rubin’s rules.

Implementation factors are processed according to the manual of the measurement instrument. Cost-effectiveness is analyzed in a health-technology assessment.

All analyses will be performed with IBM SPSS statistics 25 and R version 4.04 or higher, based on 95% confidence intervals (*p* < 0.05), and if necessary will be corrected for multiple outcomes (Bonferroni correction).

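### Single-step Bonferroni is the only multiplicity correction named; Holm's step-down gives the same family-wise control and never rejects less, so the plan gives up a modest amount of power on secondary outcomes

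*Protocol article*

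**What the plan says.** The last paragraph of Statistical analysis sets the inference rule: results are "based on 95% confidence intervals (*p* < 0.05"), and "if necessary will be corrected for multiple outcomes (Bonferroni correction"). The correction is conditional. The article does not say which outcomes form the family, how many there are, or what makes correction necessary.

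There is one primary outcome; the same section describes the models "with physical activity (in minutes per week) as the primary outcome". Outcome measures and Table 1 then list many secondary outcomes without ranking them. They cover sedentary time, diet, sleep, substance use, six physical measures (counting systolic and diastolic pressure separately), quality of life and costs. For the Brief Symptom Inventory (BSI) the Psychiatric symptoms section speaks of "examining scores for 9 symptom dimensions", and Table 1 repeats this as "Total scores for 9 symptom dimensions". No BSI overall score is listed.

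**The concern.** The article commits to a specific procedure, so the choice can be reviewed as it stands. Bonferroni tests every outcome in a family of m at 0.05/m, whatever the other results show. Holm starts at the same threshold and relaxes it after each rejection. It makes no extra assumption about how the outcomes are correlated. In a trial of about 100 people with a long list of secondary outcomes, each test at 0.05/m has low power for moderate effects, so power that can be recovered for free is worth having. What is at stake is how many real secondary effects are declared once a first one has been found.

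**Working it through.** **The plan's own figure.** Sample size states: "A sample size of 98 participants is necessary to detect an average effect (f^2^ = 0.15) in a linear regression analysis with 80% power". The model there has six predictors and the test level is 5%. For the overall F test with six predictors, the noncentrality is f² × N = 0.15 × 98 = 14.7, with 6 and 98 − 7 = 91 degrees of freedom. At alpha 0.05 the power is 0.804, so 98 is reproduced exactly. No allowance for multiplicity enters it, and nothing below changes it.

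**Why Holm is never worse.** Order the p-values from smallest to largest. Holm rejects the k-th as long as it and all smaller ones satisfy p(k) ≤ 0.05/(m − k + 1).
- Each of these thresholds is at least 0.05/m, so every Bonferroni rejection is also a Holm rejection.
- Suppose m0 hypotheses are truly null. When the first of them is wrongly rejected, at least m0 hypotheses remain in the sequence, so its p-value is at most 0.05/m0. The union bound over m0 nulls gives an error of at most 0.05, whatever the correlation. This is the bound that justifies Bonferroni.
- The first threshold is 0.05/m under both, so the chance of at least one rejection is identical.

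**Family size (assumed).** One count from Table 1 is: sedentary time 1, diet 2, sleep 2, substance use 6, physical health 6, BSI 9, EQ-5D 2. The sum is 1 + 2 + 2 + 6 + 6 + 9 + 2 = 28. Counting seven substance classes and adding costs gives 30. Neither number is stated in the article.

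**Power of one Bonferroni test.** Take m = 28 and 49 per arm (98/2), two-sided, with the normal approximation. The threshold is 0.05/28 = 0.00179 and the critical value is 3.124.
- 0.5 SD: 0.5 × √(49/2) = 2.475; power = Φ(2.475 − 3.124) = 26%.
- 0.6 SD: 0.6 × √(49/2) = 2.970; power = Φ(2.970 − 3.124) = 44%.

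**Holm against Bonferroni, by simulation with correlated outcomes.** The table shows mean power per truly affected outcome.

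| Setting | Share truly affected | Bonferroni | Holm | Gain (points) |
|---|---|---|---|---|
| m = 30, 50 per arm, 0.5 SD | 10% | 25.9% | 26.1% | 0.2 |
| same | half | 25.9% | 27.5% | 1.6 |
| same | all | 25.9% | 30.9% | 5.0 |
| m = 28, 49 per arm, 0.6 SD | half (14) | 44.5% | 47.5% | 3.0 |
| same | all | 44% | 54% | 10 |

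A run at m = 28 gave the same range: about 0.2 to 5 points at 0.5 SD and 0.4 to 10 points at 0.6 SD. In the m = 30 case with all outcomes affected, the chance of at least one rejection was 96.3% under both methods.

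**A larger effect.** The plan's f² of 0.15, read as a two-group difference, is 2 × √0.15 = 0.775 SD. At m = 30 with all outcomes affected, mean power rises from 76.6% to 89.9%, which is about 13 points. With half affected it rises from 76.7% to 80.5%, which is 3.8 points.

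**The case against.** Bonferroni is valid and only conservative, and this is an efficiency preference about secondary outcomes. That stands. There is one primary outcome, so the main conclusion does not depend on the choice. The gain is small unless many outcomes truly respond. The section also bases inference on confidence intervals, and Bonferroni has simple matching simultaneous ones (at m = 28, level 1 − 0.05/28 = 99.82%), which Holm lacks. That is a real but small cost.

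Three stronger readings are tempting, and the article does not support them.

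- *A reader might infer that Bonferroni is to be applied across the nine BSI dimensions and both weight and BMI.* These are listed as outcomes, but the correction is conditional and no family is defined. Setting the family may also be left to an analysis plan that is not shown.
- *A reader might infer that a broad improvement in symptoms would usually be missed.* The 26% is the power for one dimension. If all nine shift by 0.5 SD, with correlations of 0.4 to 0.6 and 49 per arm, at least one reaches 0.05/28 in 63% to 74% of trials. A BSI total tested at 0.05/20 (nine scores replaced by one, 28 − 8 = 20) has 52% to 73%, which is no better.
- *A reader might infer that a BSI total would be free.* It changes the question. If one dimension alone shifts by 0.6 SD (50 per arm), the total has power below 1% at 0.05/21, against 44% for that dimension at 0.05/30. The total offers a single interpretable answer, which is a trade-off for the investigators to weigh.

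Counting weight and BMI once, because BMI is calculated from weight, moves m from 28 to 27 and power at 0.5 SD from 25.8% to 26.2%. That is negligible.

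**Conclusion.** The point holds as a modest improvement. The named procedure is valid but is dominated for testing by another that needs no further assumption. With about 28 secondary outcomes, 49 per arm and effects of 0.5 to 0.6 SD, the gain in mean power is about 0.2 to 0.4 points if few outcomes are affected, 2 to 3 if half are, and 5 to 10 if all are. Family size, effect sizes and correlations are assumptions, and the gain arises only where the correction is invoked. There is no gain for the first rejection and no effect on the primary outcome or the sample size.

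**What to change.** In the last sentence of Statistical analysis, name the Holm step-down correction in place of Bonferroni. Report unadjusted 95% confidence intervals beside Holm-adjusted p-values, and state that the intervals are unadjusted, because the two can disagree for an individual outcome.

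The cost is a few words and one line of code. Study status says that data collection was ongoing at submission, so if the outcome data have not yet been analysed the change can still be made in advance. An overall BSI score may be considered as an option, with its trade-off stated; this change does not require it.

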### Study status

Data collection is ongoing at the time of this manuscript submission and recruitment is expected to be completed in the first half of 2025.

## Discussion

This study protocol is designed to investigate the (cost-)effectiveness and implementation of the *Combined Lifestyle Intervention for Outpatients with SMI (GOAL!)* in the Netherlands. *Combined Lifestyle Interventions (CLIs)* are successfully implemented in the Netherlands and showed improvements in lifestyle behaviors changes and health outcomes in the general population, but people with SMI are often excluded from these programs [31, 63]. GOAL! builds on previous successful CLIs, based on the principles of the effective *Diabetes Prevention Programs* [29, 30, 36]. These principles are also recognized as the “gold standard” for people with SMI when their specific needs are considered [4, 36]. GOAL! addresses a gap identified by people with lived experience, relatives and healthcare practitioners by providing a more suitable lifestyle intervention for outpatients with SMI.

Physical activity is the core of the GOAL! program and holds the most substantial evidence for improving overall health among all lifestyle behaviors [13]. Therefore, the primary outcome of this study is the change in physical activity levels. Nevertheless, we assess a variety of lifestyle and health outcomes. In addition, in complex intervention research, such as in this study, it is crucial to examine outcomes that are most valuable for decision making by stakeholders involved in the implementation, beyond those that can be answered with the greatest certainty [64]. In this study we assess not only the effectiveness of the intervention but also its societal impact, working elements, and interactions with the implementation context by evaluating barriers and facilitators to implementation and the cost-effectiveness.

The strengths of this study include the investigation of a lifestyle intervention specifically tailored to the needs of people with SMI, as identified by recent literature [4, 33, 34, 36] and including the perspectives of people with lived experience, relatives, and healthcare professionals. GOAL! provides long-term guidance of various certified professionals with expertise in mental health, who support individuals in overcoming challenges (e.g., motivational barriers, physiological complaints) that may arise during the program. Furthermore, the content of the sessions and coaching is focused on multiple lifestyle behaviors and is tailored to the participants’ options, needs, and goals, with a strong emphasis on transfer to the community setting. This tailored, long-term, and community-based approach enhances the prospects of intervention success.

Second, the intervention of GOAL! and the design of the study are co-created with peer support workers and relatives’ perspective, insurers and community-based organizations (e.g., municipalities, and welfare organizations). Aside from its contribution to relevance and validity, these collaborations will be valuable for potential further implementation and scale-up if GOAL! is shown to be effective.

A third strength of this study is the evaluation of a variety of outcome measures, providing a comprehensive understanding of health changes. Assessing changes not only in physical health but also in mental well-being is certainly of added value in this population. While lifestyle interventions in the general population are strongly focused on weight loss, these interventions can have an effect on several health-related outcomes, which is especially relevant for people with SMI.

Finally, by identifying the facilitators and barriers to implementation, we can optimize both the program and its implementation process. This effectiveness-implementation type 1 hybrid design is a notable strength, as it facilitates the linkage between effectiveness and implementation which is currently highly needed in this field [65]. It provides a comprehensive understanding of the underlying mechanisms behind intervention success and failure. This approach enhances external validity and supports decision making about further implementation, thereby increasing the practical impact of the findings [41].

Several limitations should be considered within the protocol of this study. First, it is challenging to include people with SMI in intervention research because of illness and healthcare-related complexities. People with SMI often face motivational barriers, self-stigma, psychological complaints, or medication side effects, potentially leading to low enrollment, low adherence, and high dropout rates [33, 34, 66]. Furthermore, healthcare practitioners may encounter inconsistencies in defining who meets the criteria for severe mental illness, organizational barriers (e.g., changes in work practices), and stigma (e.g., negative beliefs and attitudes towards people with SMI, leading to the exclusion of potential participants) [67, 68], which can lead to selection bias.

Second, participants are asked to answer many questions at each measurement point, which can be perceived as burdensome. Some questionnaires may also be difficult to answer or may include sensitive topics. To address these issues, questions can be answered face-to-face or via an online questionnaire, measurements can be spread over multiple sessions, and participants are allowed to skip questions.

Third, for GOAL! participants, half of the questionnaires are administered by the lifestyle coach and the other half by the research team, leading to variability in the data for the outcome measures. However, this is minimized by using as many validated instruments as possible and standardizing measurements and training and consultation throughout the process.

Lastly, the implementation of GOAL! takes place in a select region of the Netherlands, which may limit the generalizability of the findings. In addition, because the control group is recruited in other regions, various contextual factors may influence outcomes. However, this approach helps prevent contamination, and by evaluating the implementation and considering these contextual factors, we aim to gain insights into context-specific barriers, facilitators and processes. This understanding will assist in the interpretation of the outcomes and potential implementation of GOAL! in other regions.

The results of this study will provide a comprehensive understanding of the effectiveness and implementation of GOAL!, serving as essential input for informed decision-making regarding the future integration of lifestyle interventions into outpatient care for people with SMI.

## Data Availability

No datasets were generated or analysed during the current study.

## Abbreviations

ASSIST-Lite: Alcohol, Smoking and Substance Involvement Screening Test Lite
BSI: Brief Symptom Inventory
CLIs: combined lifestyle interventions
EQ-5D-3 L: Euro-Qol-5D-3 L
GOAL!: Combined Lifestyle Intervention for Outpatients with severe mental illness
HTA: Health Technology Assessment
LMMs: linear mixed models
MIDI: Measurement Instrument for Determinants of Innovation
SCOPA-sleep: Scales for Outcomes in Parkinson’s disease sleep
SIMPAQ: Simple Physical Activity Questionnaire
SMI: severe mental illness
TIC-P: Treatment Inventory of Costs in Patients with psychiatric disorders
QALY: quality-adjusted life years
